### **5.3. Random assignment and adjustment factors**

Upon enrollment, each patient will be randomly assigned to a treatment by [name], Department of Preventive Medicine, Kyushu University Faculty of Medical Sciences. Random assignment will be performed using a minimization method with four factors as assignment adjustment factors: pathologic stage (IA(T1bN0M0)/stage IB or stage II or stage IIIA), histologic type (non-squamous or squamous cell carcinoma (if difficult to determine, non-squamous should be used)), EGFR mutation (mutated, unmutated or unknown), and institution.

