##### Starting dose and starting method

The daily dose of S-1 is calculated according to body surface area from Table 1. “S-1 Initial standard dose and one-step dose reduction” and divided equally into two portions and administered orally after breakfast and dinner. If the creatinine clearance (CCr) at the time of enrollment is between 40 mL/min and 60 mL/min, S-1 should be started at a dose reduced by one step from the initial standard dose according to Table 1. The baseline weight is defined as the weight in which initial dose was calculated before chemotherapy. If the weight is reduced by more than 10% from the baseline, recalculate the baseline weight and use the weight at the time of recalculation as the baseline weight thereafter.

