**Table 5. Dose reduction levels (dose reduction methods for S-1)**

| Body surface area                             | At the start of treatment
(FT equivalent) | Dose reduction level |                        |                        |                        |
|-----------------------------------------------|----------------------------------------------|----------------------|------------------------|------------------------|------------------------|
|                                               |                                              | -1                   | -2                     | -3                     | -4                     |
| $< 1.25\text{ m}^2$                           | 80 mg/day                                    | 50 mg/day            | Cessation of treatment | -                      | -                      |
| $\geq 1.25\text{ m}^2$ and $< 1.5\text{ m}^2$ | 100 mg/day                                   | 80 mg/day            | 50 mg/day              | Cessation of treatment | -                      |
| $\geq 1.5\text{ m}^2$                         | 120 mg/day                                   | 100 mg/day           | 80mg/day               | 50 mg/day              | Cessation of treatment |

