### 12.2. Evaluation method

Treatment completion rate (Feasibility)

Definition of treatment completion

Patients who have completed six months of treatment with S-1 as postoperative chemotherapy with a dose reduction/withdrawal ratio of at least 70% while following the dose reduction/withdrawal criteria specified in the protocol are defined as those who have completed the protocol treatment (completed administration).

S-1 actual total dose/planned total dose ratio

Percentage of doses administered (%) = Total actual prescriptions during the entire dosing period (mg)/total scheduled doses (mg) x 100

However, total expected dose = initial dose (mg/day) x total expected days (days), and

Defined as the sum of the actual doses taken during the entire treatment period (mg) =  $\Sigma$  (total doses taken up to 6 months or until treatment discontinuation), where  $\Sigma$  (total doses taken up to 6 months or until treatment discontinuation).

Finally, for the primary endpoint, the proportion of patients who “completed the protocol” to all eligible patients will be calculated, excluding those who discontinued or dropped out of the protocol due to recurrence. The completion rate at 9 months, 1 year, etc. of protocol treatment will also be calculated.

Recurrence-free survival (RFS)

The period beginning on the date of registration and ending on the earlier date on which the patient is determined to have relapsed or the date of death from any cause.

The term “recurrence” includes both diagnostic imaging and clinical relapse, which is defined as an exacerbation of a disease condition that is not diagnosed by imaging. In the case of a recurrence determined based on imaging diagnosis, the date of recurrence is the date of the examination that performed the imaging test. A period of elevated tumor markers alone shall not be considered as recurrence, but the date of examination when recurrence is confirmed by diagnostic imaging or the date of clinical judgment of recurrence due to worsening of the disease condition shall be considered as recurrence.

In the case of a surviving patient who has not been judged to have relapsed, the last date of confirmation of survival shall be the date of termination. (Survival confirmation by phone call is also acceptable, but the fact that survival confirmation was made must be recorded in the medical record.)

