### 13.3. Basis for setting the number of cases

When conducting an analysis of the primary endpoint using the “Definition of the percentage of treatment completion” in the “Evaluation Methodology” section of the endpoints, cases of protocol discontinuation due to relapse should be treated as discontinuations (dropouts), and are not appropriate as eligible cases for the analysis. The percentage of patients who “completed treatment” was calculated based on the number of patients who were excluded from the total number of eligible cases.

In the LOGIK0601 study of S-1 80 mg/m^2/day 2-week administration followed by 1-week rest (6 months administration) in patients with Stage IB or more completely resected non-small cell lung cancer, treatment completion was 56.7% (95% CI: 37.4–74.5, relative dose rate 73.9) and the completion rate in patients 70 years and older was 42.9% (6/14). On the other hand, although the data are not available for elderly patients, the use of S-1 every other day (1 year) after gastric cancer surgery resulted in 19.6% and 13.7% higher compliance and RDI, respectively, than the usual administration regimen (1 year) (91.8% vs 72.2% and 81.2% vs 67.5%, respectively).

Assume that 55% of the patients in the better group and 40% of the patients in the worse group complete treatment for 6 months with the biweekly or 2-week administration followed by 1-week rest method. Based on the selection theory, 37 cases in each group are required to detect this 15% difference with a 90% probability of correct selection. Assuming dropout cases, a total of 100 cases are required. The expected annual enrollment is 50 cases, and the enrollment period is 2 years.

In order to achieve ITT analysis, Kaplan-Meier curves for the actual total number of days of S-1 administration in each case were drawn for all enrolled patients. An event is considered to have occurred at the time of discontinuation due to S-1 toxicity. If the drug is discontinued due to complications (recurrence, second cancer) that are not directly related to S-1, the event is considered to have occurred at that time.

The continuation rate calculated from the Kaplan-Meier curve will also be evaluated as a secondary measure of compliance with the study treatment.

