### 13.4. Decision criteria for standard treatment (S-1 administration) based on the results

This study was designed to verify that alternate-day administration is a superior method of administration with better continuity than the daily administration method. However, the difference in administration continuity alone does not necessarily mean that the true objective of adjuvant chemotherapy, namely, survival benefit, is achieved.

Therefore, at the end of the trial, the decision criteria for selecting either study arm for future Phase III trials shall be as follows.

- (1) If the six-month completion rate for both groups is less than 40%, we conclude that both groups are not promising adjuvant chemotherapy in this study.
- (2) If the completion rate of six-month treatment in one group exceeds 40% and is more than 15% higher than that in another group, we conclude that the treatment in the group with the higher completion rate of six-month treatment is the most promising adjuvant chemotherapy in the study and is more suitable for the administration of S-1 in future Phase III trials.
- (3) If the completion rate in one group is greater than 40% and the difference between one group and the other is within 15%, the two groups will not be directly compared based on retention rate numbers alone, but rather on toxicity, quality of life, convenience, cost, retention rate after 6 months, recurrence-free survival, and survival rate to determine which is more suitable as S-1 therapy in future Phase III trials.

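### Minimisation omits renal function and starting dose, which the dose tables link to the completion endpoint; report the 6-month completion difference stratified by one of them beside the raw rates

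*Protocol*

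**What the plan says.** **Allocation (5.3).** "Random assignment will be performed using a minimization method with four factors as assignment adjustment factors". Stage and histologic type come first, and the list ends with "EGFR mutation (mutated, unmutated or unknown), and institution". CCr, body surface area and starting dose are not listed.

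**Starting dose (6.2.1 and 6.3.1).** In Arm A, for CCr 40 to 60 mL/min at enrolment, "S-1 should be started at a dose reduced by one step from the initial standard dose according to Table 1". Arm B has the same rule with the same steps (Table 8). Patients who start lower for this reason may not be escalated in either arm.

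**Dose ladder (Tables 5 and 12).** The floor is 50 mg/day, and the step below it is "Cessation of treatment". Creatinine of 1.2 mg/dL or more is itself a reduction criterion (Tables 4 and 11).

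**Primary endpoint (12.2).** A completer finishes six months with at least 70% of the planned dose, where "total expected dose = initial dose (mg/day) x total expected days (days"). Patients who stop for recurrence are left out.

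**Decision (13.4).** Rule (2) selects an arm whose completion rate "exceeds 40% and is more than 15% higher than that in another group". If the difference is within 15 points, rule (3) turns to toxicity, quality of life, convenience, cost, later retention, recurrence-free survival and survival.

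**The concern.** Three of the four factors (stage, histology, EGFR) chiefly predict recurrence, and patients who stop for recurrence leave the primary denominator. The baseline quantity that the protocol itself connects to the 70% threshold, starting dose as set by CCr and body surface area, is left to chance. The same toxicity followed by the same one-step reduction can leave one patient a completer and another not, depending on where each began on the ladder.

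Rule (2) uses raw rates in a small trial. If one arm happens to receive more patients low on the ladder, part of the observed difference reflects case mix and not schedule. At stake is which side of the 15-point line this one trial falls on, and so whether completion alone or the wider judgement in rule (3) picks the regimen for phase III.

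**Working it through.** **1. The plan's own figure.** Section 13.3 reads: "Assume that 55% of the patients in the better group and 40% of the patients in the worse group complete treatment for 6 months", and concludes that "37 cases in each group are required to detect this 15% difference with a 90% probability of correct selection".
- Normal approximation: n = z²(p₁q₁ + p₂q₂)/δ² = 1.2816² × (0.2475 + 0.2400)/0.15² = 35.6. With pooled variance it is 36.4.
- Exact binomial at 37: P(better arm ahead) 0.882 plus half of P(tie) 0.040 gives 0.902. The figure reproduces.

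**2. Dose ladder against the 70% rule.** Share of the initial daily dose left after each reduction:

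| Body surface area | CCr | Start (mg/day) | One step | Two steps |
|---|---|---|---|---|
| < 1.25 m² | ≥ 60 | 80 | 50/80 = 62.5% | cessation |
| < 1.25 m² | 40–60 | 50 | cessation | – |
| 1.25 to < 1.5 m² | ≥ 60 | 100 | 80/100 = 80% | 50% |
| 1.25 to < 1.5 m² | 40–60 | 80 | 50/80 = 62.5% | cessation |
| ≥ 1.5 m² | ≥ 60 | 120 | 100/120 = 83% | 67% |
| ≥ 1.5 m² | 40–60 | 100 | 80/100 = 80% | 50% |

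An 80 mg starter with perfect intake needs f + 0.625(1 − f) ≥ 0.70, where f is the fraction of the period at full dose. So f ≥ 0.20, about day 36 if six months is taken as 182 days. An earlier reduction rules out 70%. In the two lower size bands CCr changes the result of the first reduction; at 1.5 m² or more it matters only from the second.

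**3. Chance imbalance.** The protocol gives neither the prevalence of CCr 40–60 nor completion by CCr. Assumed: prevalence p of 30–60%, completion gap of 20–30 points between CCr groups, and CCr left to simple randomisation.
- SD of the imbalance at 50 per arm = √(2p(1 − p)/50) = 0.092 (p = 0.3), 0.100 (0.5), 0.098 (0.6).
- P(imbalance ≥ 15 points, either direction) = 10%, 13%, 13%.
- P(imbalance ≥ 20 points) = 3–5% by the normal approximation; exact binomial gives 4–6%.
- At 37 per arm, p 0.3–0.5: SD 0.107–0.116, P(≥ 20 points) 6–8%.

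**4. Shift in the completion difference** = imbalance × gap.
- 15 points: 0.15 × 0.20 = 3 points, up to 0.15 × 0.30 = 4.5 points.
- 20 points: 0.20 × 0.20 = 4 points, up to 0.20 × 0.30 = 6 points.

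**5. Given a 20-point imbalance against the better arm, at 37 per arm.** Correct selection falls from 0.902 to 0.828 (20-point gap) or 0.781 (30). P(observed difference above 15 points) falls from 0.507 to 0.370 or 0.307.

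**6. Averaged over randomisation.** Without the factor, correct selection stays at 0.902–0.903, because the binomial calculation already contains this variation. With perfect balance it is 0.906–0.907 (20-point gap) or 0.911–0.913 (30). In simulation at 40% prevalence and 37 per arm, the Mantel-Haenszel difference gives about the same gain (0.4 to 1 point) and falls on the other side of the 15-point line from the raw difference in about 6–10% of trials.

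**The case against.** The strongest reply is that nothing here is an error. Randomisation may leave covariates to chance, and the selection probability already allows for it. Steps 1 and 6 confirm this, and that part stands in full.

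Other parts also stand:
- Institution is not a tumour factor and may bear on treatment continuation, which depends partly on physician discretion.
- Rule (3) uses recurrence-free survival and survival. With true rates of 55% and 40%, the observed difference exceeds 15 points only about half the time (0.507), so the tumour factors matter to selection and should not be traded away.
- The size and direction of the CCr effect are unknown. The dose ratio uses the patient's own starting dose, so a lower start also lowers the denominator.
- Balancing CCr does not fully balance starting dose: an 80 mg starter can come from either CCr group.
- Body surface area and CCr or creatinine are recorded at enrolment (11.3), so an imbalance could be seen. The statistical analysis plan is not at hand and may contain an adjusted analysis.

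What the reply does not remove is that 13.4, where the decision rule is fixed, compares raw rates with a numerical line, while the protocol's own tables identify a baseline quantity that can move them.

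**Conclusion.** The point holds as a modest gain in precision and credibility. Under the assumed 20–30 point gap and 30–60% prevalence, imbalances of 15 to 20 points shift the completion difference by 3 to 6 points against a 15-point line. They are uncommon at 50 per arm (10–13% for 15 points or more, 3–5% for 20 or more), and only half of them work against the better arm.

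A reader might infer more: that the allocation biases the comparison, that 37 per group is too few, or that starting dose decides completion. The documents support none of these. Imbalance favours neither arm on average and the sample size reproduces. The dose tables show a mechanism, clear below 1.5 m² and weak at the first step above it, but the protocol reports no completion rates by CCr or starting dose.

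**What to change.** In 13.3/13.4, pre-specify that the 6-month completion difference is also estimated by the Mantel-Haenszel method, stratified by registration CCr group (40 to under 60 v 60 or more) or by starting dose, and reported beside the raw rates whenever the 15-point rule is applied. Choose the stratifier in advance: starting dose follows the mechanism more closely, while CCr has only two strata. Tabulate completion by starting dose (50, 80, 100, 120 mg/day) in each arm. The data are already collected, so the cost is a little programming.

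For patients still to be enrolled, CCr group may be added in 5.3 as a further minimisation factor, keeping the tumour factors that rule (3) relies on. The cost is a short amendment and slightly looser balance across the existing factors. No dose or treatment rule changes.

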## 6. Protocol treatment

### 6.1. Overview

The alternate-day administration of S-1 and 2-week administration of S-1 followed by 1-week rest are defined as protocol treatment in this study. As a rule, protocol treatment will be initiated within 1 week after enrollment and within 8 weeks after surgery. If more than 8 weeks have elapsed since surgery, the data center will be contacted to confirm whether protocol treatment can be started, and if so, it will be initiated. After initiation, the reason why the treatment could not be started within 8 weeks should be noted in the comment section of the “Report of Study Initiation and Pre-Treatment Discontinuation”. TS-1 should be TS-1 combination capsules T20, T25, TS-1 combination granules T20, T25, and TS-1 combination OD tablets T20, T25 (Taiho Pharmaceutical Co).

### 6.2. Arm A: S-1 alternate-day administration method

#### 6.2.1. Treatment schedule for Arm A (S-1 alternate-day administration method)

Treatment should begin within 8 weeks after surgery.

##### Administration Schedule

The first dose of S-1 should be initiated on Monday, Wednesday, Friday, or Sunday (the specified day of the week); Day 1 is defined as the day on which S-1 is initiated.

If S-1 cannot be administered after breakfast, it may be started after dinner. Even if S-1 is started after dinner, the day should be defined as the day on which S-1 is initiated, and the next dose should be taken on the specified day of the week.

(e.g., if taken on Friday evening, the next dose will be given on Sunday morning)

S-1 should be administered on Mondays, Wednesdays, Fridays, and Sundays and should be continued until one of the criteria for discontinuation of treatment is met. **S-1 should not be administered other than the specified day.**

- If administration cannot be started more than 28 days after the last day of administration, this study treatment will be discontinued (day 1 will be the day after the last dose). The same day of the week 4 weeks after the last dose is acceptable).

[figure not shown]

##### Starting dose and starting method

The daily dose of S-1 is calculated according to body surface area from Table 1. “S-1 Initial standard dose and one-step dose reduction” and divided equally into two portions and administered orally after breakfast and dinner. If the creatinine clearance (CCr) at the time of enrollment is between 40 mL/min and 60 mL/min, S-1 should be started at a dose reduced by one step from the initial standard dose according to Table 1. The baseline weight is defined as the weight in which initial dose was calculated before chemotherapy. If the weight is reduced by more than 10% from the baseline, recalculate the baseline weight and use the weight at the time of recalculation as the baseline weight thereafter.

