**Table 1. S-1 initial standard dose and one-step dose reduction**

| Body surface area                              | Initial standard dose (FT equivalent)
(CCr ≥ 60) | Dose reduction level -1
(40 ≤ CCr < 60) |
|------------------------------------------------|-----------------------------------------------------|--------------------------------------------|
| < 1.25 m                           | 80 mg/day                                           | 50 mg/day                                  |
| ≥ 1.25 m  and < 1.5 m  | 100 mg/day                                          | 80 mg /day                                 |
| ≥ 1.5 m                            | 120 mg/day                                          | 100 mg /day                                |

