**6.2.5. Criteria for dose reduction (Arm A)**

When resuming administration in patients with adverse events that meet the dose reduction criteria specified in Table 4, the dose should be reduced one step at a time according to “Dose reduction levels” in Table 5. However, the minimum dose of S-1 is 50 mg/day, and the dose will not be increased again after a dose reduction. For adverse events other than those listed in Table 4, the S-1 dose may be reduced at the discretion of the treating physician, again in accordance with the dose reduction levels listed in Table 5.

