### 6.3. Arm B: S-1 2-week administration followed by 1-week rest method

#### 6.3.1. Treatment schedule for Arm B (S-1 2-week administration followed by 1-week rest method)

**Administration cycle:** Oral administration every day for 14 consecutive days from Day 1 (after dinner on Day 1 to after breakfast on Day 15)

The drug is then withdrawn for 7 days, and this is repeated every 3 weeks for one course.

**End date of treatment:** Administration should be performed until the total treatment period from the protocol treatment start date has reached 12 months. No new courses should be started after the same calendar day 12 months after the protocol treatment start date. The final course of treatment should be administered until a date equivalent to day 14.

[figure not shown]

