#### Starting dose and starting method

The daily dose of S-1 is calculated according to body surface area from Table 8. “S-1 initial standard dose and one-step dose reduction” and divided equally into two portions and administered orally after breakfast and dinner. If the creatinine clearance (CCr) at the time of enrollment is between 40 mL/min and 60 mL/min, S-1 should be started at a dose reduced by one step from the initial standard dose according to Table 8. If the patient’s body weight has decreased by more than 10% from the baseline, the dose is recalculated and the baseline body weight is considered to be the weight at the time of recalculation.

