**Table 8. S-1 initial standard dose and one-step dose reduction**

| Body surface area                              | Initial standard dose (FT equivalent)
(CCr ≥ 60) | Dose reduction level -1
(40 ≤ CCr < 60) |
|------------------------------------------------|-----------------------------------------------------|--------------------------------------------|
| < 1.25m                            | 80 mg/day                                           | 50 mg/day                                  |
| ≥ 1.25 m  and < 1.5 m  | 100 mg/day                                          | 80 mg/day                                  |
| ≥ 1.5m                             | 120 mg/day                                          | 100 mg/day                                 |

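### After a weight loss above 10%, Arm A (6.2.1) resets only the baseline weight while Arm B (6.3.1) recalculates the dose: very probably a wording slip in a dosing rule

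*Protocol*

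**What the plan says.** Protocol 6.2.1 (Arm A), under the starting dose, sets the daily dose from body surface area using Table 1. It then defines the reference weight: "The baseline weight is defined as the weight in which initial dose was calculated before chemotherapy". For a loss of more than 10% from that reference, the instruction is to "recalculate the baseline weight and use the weight at the time of recalculation as the baseline weight thereafter". The dose is not mentioned.

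Protocol 6.3.1 (Arm B), under the same sub-heading and for the same trigger, says "the dose is recalculated and the baseline body weight is considered to be the weight at the time of recalculation".

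The two dose tables, "Table 1. S-1 initial standard dose and one-step dose reduction" and "Table 8. S-1 initial standard dose and one-step dose reduction", hold identical bands (below 1.25, 1.25 to below 1.5, and 1.5 m² or more) and identical doses: 80, 100 and 120 mg/day at standard dose, and 50, 80 and 100 mg/day for creatinine clearance (CCr) from 40 to below 60 mL/min.

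**The concern.** One event triggers two different printed actions depending on the arm. In Arm B the dose follows the patient's new body size. In Arm A, read literally, only the reference for the next 10% check moves and the dose stays where it was. No reason for a difference between arms is given, and none follows from the dose tables.

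This is an operative dosing instruction for a cytotoxic drug in patients aged 75 or older. A site that follows 6.2.1 to the letter would leave a patient who has fallen into a lower body-surface band one step above the dose that Table 1 gives for that patient's size.

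**Working it through.** **Is there another Arm A rule that fills the gap?** No. Sections 6.2.2 to 6.2.7 cover start, continuation, resumption, dose reduction, escalation and completion; none ties the dose to weight change. Section 7.1 and section 8 do not either.

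**What was intended?** Three features of 6.2.1 point to dose recalculation. Baseline weight is defined there as the weight behind the initial dose. Its only use in the protocol is the 10% trigger, so resetting it alone achieves nothing except a new reference for the next trigger. And a weight is measured, not calculated, so a time of recalculation presupposes that something else, the dose, was recalculated.

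**Dose consequence within Arm A.** Arm A doses 4 days a week ("S-1 should be administered on Mondays, Wednesdays, Fridays, and Sundays"), so weekly dose = daily dose × 4.

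| Band crossed (Table 1) | Literal 6.2.1 | Recalculated | Excess |
|---|---|---|---|
| Below 1.5 m², standard start | 120 × 4 = 480 mg | 100 × 4 = 400 mg | +20% |
| Below 1.25 m² standard, or below 1.5 m² CCr-reduced | 100 × 4 = 400 mg | 80 × 4 = 320 mg | +25% |
| Below 1.25 m², CCr-reduced start | 80 × 4 = 320 mg | 50 × 4 = 200 mg | +60% |

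**Dose consequence between arms.** Arm B doses 14 days in 21 ("Oral administration every day for 14 consecutive days from Day 1"), so average weekly dose = daily dose × 14/3.

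| Daily dose, literal A v recalculated B | Arm A per week | Arm B per week | A relative to B |
|---|---|---|---|
| 120 v 100 | 480 mg | 100 × 14/3 = 466.7 mg | +2.9% |
| 100 v 80 | 400 mg | 80 × 14/3 = 373.3 mg | +7.1% |
| 80 v 50 | 320 mg | 50 × 14/3 = 233.3 mg | +37.1% |

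With the same daily dose in both arms the ratio is (4/7)/(14/21) = 0.857, so Arm A would be 14.3% lower each time. Only the 80 v 50 case is a large gap between arms, and it needs a CCr-reduced starter who falls below 1.25 m².

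**How many patients?** The protocol gives no body-surface formula, no body-surface distribution and no frequency of weight loss, so everything here is assumption.

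- Body surface proportional to weight to the power 0.425 to 0.5: a 10% loss multiplies it by 0.9^0.425 = 0.956 to 0.9^0.5 = 0.949.
- Starters who change band lie just above a cut-off, within 1.25/f − 1.25 = 0.057 to 0.068 m², or 1.50/f − 1.50 = 0.069 to 0.081 m², where f is that factor.
- If body surface is uniform over 1.2 to 1.8 m², the share is (0.057 + 0.069)/0.6 = 0.21 to (0.068 + 0.081)/0.6 = 0.25. If it is normal with mean 1.45 to 1.60 and SD 0.12 to 0.18, the share is 0.168 to 0.296.
- If 5% to 15% of an arm of 50 (half of the 100 planned) lose just over 10%: 50 × 0.05 × 0.168 = 0.42 to 50 × 0.15 × 0.296 = 2.2 patients.

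**The case against.** The best reply is that 6.2.1 can be read only one sensible way. Its paragraph starts from calculating the dose, ties baseline weight to that dose, and makes no sense unless the dose is what is recalculated. An investigator would probably do the right thing, and then the arms do not differ in practice. The slip may also have arisen in translation: the English text carries Japanese tracked-change residue in 12.2, and any source-language text used at sites may be correct. That reply stands as a reason to rate the point low. It does not make the sentence right, and a multicentre protocol should not leave a cytotoxic dose rule to inference from the other arm's section.

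Safety margins also exist. Under 6.2.5, for adverse events outside Table 4, "the S-1 dose may be reduced at the discretion of the treating physician", and the adverse event definition in 9.2 is broad enough to take in unwanted weight loss. Section 7.1 allows discontinuation at the physician's judgement. Section 6.2.6 lets standard-dose starters without relevant toxicity go one step above the initial dose after 43 days, so one step high lies within what the protocol tolerates for them. All of this limits the harm. But the reduction is optional where Arm B's recalculation is not, and CCr-reduced starters, who face the largest gap, may not escalate.

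Finally, a recalculation from Table 1 might seem able to raise a dose already cut for toxicity: a patient who started at 120, was reduced to 80 and now falls between 1.25 and 1.5 m² would find 100 in the table. The rule in 6.2.5 against increasing the dose after a reduction prevents this, and the fix keeps that rule.

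**Conclusion.** The concern holds, as a minor one. Section 6.2.1 as printed resets a weight where 6.3.1 recalculates a dose, for the same trigger and the same dose tables. It is very probably a drafting or translation slip and not a deliberate difference between arms.

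The dose arithmetic follows from the protocol's own tables and schedules: an Arm A patient who changes band is left 20%, 25% or 60% above the recalculated dose, while literal Arm A against recalculated Arm B differs by about 3%, 7% or 37%. The count of about 0.4 to 2.2 patients in 50 rests wholly on the assumed weight loss, body-surface distribution and exponent. No effect on the six-month completion rate is claimed, and actual harm is not shown, because sites may well have read the rule as intended.

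**What to change.** In 6.2.1, replace the instruction to recalculate the baseline weight with one to recalculate the dose from the current body surface area (Table 1). Keep the rest of the sentence, which makes the weight at that time the new baseline. The rule then matches 6.3.1. Leave 6.3.1, the rules against re-increase after a reduction (6.2.5 and 6.3.4) and the escalation rules of both arms unchanged.

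The cost is one phrase in one sentence. No extra data are needed, because weight is already measured every 1 to 2 weeks during treatment (11.4).
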